### Criteria for withdrawal from the study

- Severe adverse reaction potentially attributable to benznidazole or not.
- Any situation that may put the safety of the patient at risk, according to the judgment of attending physicians.

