## Patient recruitment

Patients found to be seropositive for *T. cruzi* and their parents or guardians will be summoned for a meeting conducted at the nearest rural school or healthcare post. Local physicians will communicate treatment benefits and eventual risks of ADRs to the patients. A locally adapted plan for monitoring ADR and medication adherence will be discussed and agreed upon.

Prior to the onset of treatment with benznidazole, the attending physicians will evaluate the patients’ clinical status at the healthcare posts or schools immediately before treatment (0 days posttreatment initiation, dpt) and record the results in an individual clinical history. Each clinical evaluation will include a semiologic exam, an electrocardiographic exam, and clinical laboratory tests to assess hematocrit and hemoglobin levels, platelets, white cell counts, alanine aminotransferase, aspartate aminotransferase and alkaline phosphatase, cholesterol, uremia, serum creatinine and serum proteins at the local hospital. Women in reproductive age will be tested for pregnancy. A blood sample aliquot will be kept for serological and molecular diagnosis as described above.

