## Follow up

Monitoring of medication adherence and ADRs will be conducted by local healthcare agents in five weekly appointments at the health post or at the patient’s home where they will record the patient’s body weight and temperature, and the number of benznidazole pills remaining. The patients’ parents or guardians will notify the healthcare agents the onset of any adverse drug-related reaction, sign or symptom, or may directly communicate with the coordination team by cell phone. The research team will keep a treatment diary to record the doses administered, its timing, and any symptoms or problems related to treatment.

All ADRs detected during drug administration (i.e., type, date of onset and remission, duration, and specific treatment indicated) will be recorded in each patient’s clinical history. Patients showing a severe or moderate, prolonged exanthema combined with fever will be transported to the local hospital for medical evaluation. Temporary suspension or benznidazole dose reduction or treatment with corticoesteroids or antihistamines may be prescribed to patients with mild or moderate reactions. Healthcare agents will follow up the evolution of ambulatory patients until remission.

The local physicians will re-evaluate the patients’ clinical status at the healthcare posts or schools 10, 20-30 and 60 dpt, and add these results to each individual clinical history. Each clinical evaluation will include a semiologic exam and clinical laboratory tests at 20-30 and 60 dpt to assess the same variables as determined at baseline. A blood sample aliquot will be kept for serological and molecular diagnosis as described above. Additional blood samples will be collected at 180 dpt for serological and molecular diagnosis of *T. cruzi* infection. All sera collected at 0, 60 and 180 dpt will be tested in parallel to assess any decay in specific antibody titers relative to baseline values.

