# Data Analysis and statistical methods

Treatment-related primary outcomes included treatment coverage (i.e., percentage of seropositive patients up to 18 years of age at serodiagnosis that were treated with benznidazole relative to the number of seropositive patients in this age group who were eligible for treatment); treatment quality (based on individual completion, medication adherence – as determined by the average percentage of benznidazole pills taken relative to those provided for each specific time period- and ADR management --percentage of patients who presented ≥1 ADR and were able to complete treatment), and therapeutic response (detection of *T. cruzi* DNA by kPCR and qPCR in patients who completed the full treatment course and had ≥80% of medication adherence). Patients with three or fewer pill counts and those withdrawn from or who abandon treatment will be excluded from adherence estimates. The therapeutic response to treatment will be essentially measured by the proportion of patients who were qPCR-negative at 180 dpt among those who had been qPCR-positive before treatment.

Statistical analysis will include Friedman’s two-way non-parametric analysis of variance for testing differences among repeated measurements of biochemical variables before treatment and at 20 and 60 dpt; Kendall’s *K* as an index of concordance; Fisher’s exact test or χ^2^ tests for investigating two by two contingency tables of independent data, and exact McNemar significance probabilities for paired data with small cell frequencies. The nominal level of statistical significance is set at a *P* value of 0.05. All tests will be performed using Stata 12.

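### The three-occasion Friedman test drops any child without a 60 dpt laboratory value, and the withdrawal criteria may tie that missing value to toxicity

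*Protocol*

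**What the plan says.** All references are to the protocol.

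- **Data Analysis and statistical methods** assigns the biochemical variables to Friedman's "two-way non-parametric analysis of variance for testing differences among repeated measurements of biochemical variables before treatment and at 20 and 60 dpt". The threshold is nominal: "The nominal level of statistical significance is set at a *P* value of 0.05". The section names no separate comparison of baseline with the first on-treatment visit for these variables, and no method for incomplete series.
- **Follow up** schedules "clinical laboratory tests at 20-30 and 60 dpt to assess the same variables as determined at baseline". The first on-treatment visit is thus a window here and a single day in the analysis section.
- **Patient recruitment** fixes the time origin. The baseline evaluation is "immediately before treatment (0 days posttreatment initiation, dpt", so 60 dpt is counted from the start of treatment.
- **Criteria for withdrawal from the study** has two entries: "Severe adverse reaction potentially attributable to benznidazole or not" and "Any situation that may put the safety of the patient at risk, according to the judgment of attending physicians". Both concern leaving the study, not only the drug. No biochemical testing after withdrawal is described.

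**The concern.** Friedman's test ranks each child's values across the occasions, so a child enters only with all three. A child withdrawn after the 20-30 dpt visit but before 60 dpt would usually have two measured values, and the test would use neither. The withdrawal criteria are about safety, so the children lost this way may be those with the larger laboratory changes.

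At stake is how a null result is read. Finding no significant change in, say, transaminases or blood counts would be taken as reassurance about the drug, although some of the children taken out for safety reasons did not contribute their on-treatment values.

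**Working it through.** The protocol states no sample size, power, variability or withdrawal rate, so there is no figure to reproduce. All numerical inputs below are assumptions.

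**1. Does one missing value remove the child?** Take four children whose values rise at every occasion, with the third value of one child missing. The test either returns no result or runs on three children. With identical ordering in all children the statistic is n(k − 1). For the three that remain this is 3 × 2 = 6.0 (P = e^(−6/2) = 0.0498); with all four complete it would be 4 × 2 = 8. The fourth child's first two values are not used.

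**2. Bias at 20-30 dpt.** Assume 25% of children have a rise of 0.7 on the log scale (e^0.7 ≈ 2.0) and the rest have none.

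- All children: mean 0.25 × 0.7 = 0.175, ratio e^0.175 = 1.19.
- 10% of all children lost, all from those affected: the affected share becomes (0.25 − 0.10)/0.90 = 0.167, the mean 0.167 × 0.7 = 0.117, the ratio e^0.117 = 1.12.
- 10% lost, being the largest observed rises: ratio 1.08 by simulation. The share of children with at least a doubling reads 5% instead of 14%.
- Losses unrelated to the laboratory value: no bias.

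**3. Power in the same model.** Between-child SD 0.35, within-child SD 0.25 (log scale), the rise present at both on-treatment visits, 80 children, 10% lost. Ranges cover repeated runs.

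| Who is lost | Friedman, nobody lost | Friedman, complete children | Paired Wilcoxon, 0 vs 20-30 dpt, all children |
|---|---|---|---|
| Largest rises | 63-66% | 27-31% | 84-89% |
| Random among affected | 63-66% | 27-31% | 84-89% |
| Random among all | 63-66% | 59-61% | 84-89% |

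Deletion accounts for the drop from the first figure to the second. The gap between the first and the third is a difference between tests on complete data and should not be charged to deletion.

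**4. A second model.** No change in children who continue; a shift of 2 units in those who stop (between-child SD 1, within-child SD 0.7); 40, 80 or 120 children. The true mean change is the share stopping × 2, that is 0.10, 0.20 and 0.40 at 5%, 10% and 20%. If every child who stops lacks the 60 dpt value, the complete-block mean is about 0.00. Rejection rates, lowest to highest over the three sample sizes:

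| Share stopping | Friedman, nobody lost | Friedman, complete children | Paired test, all children |
|---|---|---|---|
| 5% | 5-8% | 4-6% | 7-11% |
| 10% | 9-20% | 4-5% | 13-34% |
| 20% | 24-63% | 5% | 40-85% |

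At 5% stopping, deletion costs at most about 3 percentage points. If half of those who stop still attend at 60 dpt, the loss is partial: at 20% stopping, Friedman rejects in 8-21% of runs and the mean reads about 0.22 instead of 0.40.

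**5. A widespread effect.** In the first model with 80 children and 10% lost, a uniform rise with the same mean ratio of 1.19 keeps power at 96% or more under random loss; it falls from about 97% to 87% if the largest rises are lost. With a two-fold rise in half the children, power stays above 99%. The loss of power thus mostly disappears, and bias remains only where the missing values belong to children with larger rises.

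**The case against.** A reader might infer that every child who stops the drug is deleted, so that laboratory safety is judged only on children who tolerated it. The protocol does not support this, for four reasons.

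- Days are counted from treatment initiation, and Follow up does not limit the 60 dpt tests to children still on drug. Only a missing 60 dpt value causes deletion. The stated exclusion, "those withdrawn from or who abandon treatment will be excluded from adherence estimates", covers adherence and not the laboratory variables.
- Children with lesser reactions can remain and reach 60 dpt: "Temporary suspension or benznidazole dose reduction or treatment with corticoesteroids or antihistamines may be prescribed to patients with mild or moderate reactions".
- Adverse drug reactions and evaluation results go into each child's clinical history whether or not treatment is completed. Biochemical variables are not among the listed primary outcomes. One group-level test is affected, not safety reporting as a whole.
- No laboratory threshold for withdrawal is given. The reaction that Follow up describes most concretely is exanthema with fever. That withdrawn children have larger laboratory changes is plausible, but it is assumed.

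It can also be said that missing-visit handling belongs in a statistical analysis plan, which is not at hand, and that the protocol's list of tests need not be exhaustive. That limits the point without removing it. The protocol itself fixes the test, the three occasions and the withdrawal criteria, and these do not fit together for a child withdrawn between the two on-treatment visits.

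**Conclusion.** The point holds in a limited form. The one test named for the biochemical variables discards the measured values of any child without a 60 dpt result, and the withdrawal criteria give a reason why such children may differ in the direction of toxicity. The test may therefore understate an on-treatment change.

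The size cannot be derived from the protocol. It is negligible if withdrawal is rare, or if it is unrelated to the laboratory values. It reaches a loss of about half the power if 10% of children are withdrawn, all of them from the quarter who are affected. That severe end is demanding: with 80 children, 8 of the 20 affected (40%) are lost and no unaffected child is. A reader might take these figures as forecasts for this trial, or assume that the same loss of power would follow from a widespread drug effect; neither is supported. The change is worth making because it keeps data already collected and costs little.

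**What to change.** 1. Compare baseline with 20-30 dpt in every child who has both values, using the Wilcoxon signed-rank test with the median change. Compare baseline with 60 dpt separately, marking children already off drug.
2. If one overall test per variable is wanted, use a method that keeps incomplete series, such as the Skillings-Mack test or a mixed model on log values.
3. State whether children who stop treatment or are withdrawn have laboratory tests at 60 dpt. Report how many children each comparison loses and why.
4. Reconcile 20 dpt in Data Analysis and statistical methods with 20-30 dpt in Follow up.

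The cost is analysis wording, with no new data. The separate tests give two comparisons per variable instead of one. Children who stop before the 20-30 dpt visit may have no on-treatment value, and no choice of test recovers them; they should appear in the counts under item 3.

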# ethical considerations

Informed written consents will be taken as detailed above. All clinical investigations will be conducted according to the principles expressed in the Declaration of Helsinki and the regulations of the Argentine Ministry of Health and the Ministry of Health of Chaco Province.

# data confidentiality

Patient data confidentiality will be strictly ensured. Samples will be identified by alphanumeric codes. Patient data will be stored in files and computers to which only the principal investigators and co-investigators will have access.

